###### Cortical excitability

2.6.2.2.5

Cortical excitability was assessed via MEPs amplitude. Single-pulse transcranial magnetic stimulation (sTMS) was delivered to the primary motor cortex (M1) using the MagTD device at 100%–120% of each participant's resting motor threshold (RMT). MEPs were recorded from the right abductor pollicis muscle at rest, and peak-to-peak amplitudes were measured. Six consecutive pulses were applied at 5-s intervals, with the mean amplitude serving as the excitability index. To account for inter-individual variability, MEPs were normalized to baseline values. If baseline variability exceeded 15% between groups, analyses were adjusted using either stratification or ANCOVA with baseline MEPs as a covariate.

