#### rTMS+LI-BFRT

2.5.2

Participants will undergo a 12-week intervention consisting of three sessions per week, each lasting 60 min, combining rTMS (20 min) and LI-BFRT (40 min). The rTMS protocol is as follows: stimulation intensity of 90% of the RMT, is applied to the primary motor cortex (M1) with a stimulation frequency of 10 Hz, each sequence lasting 10 s, and an interval of 50 s. A total of 1,000 pulses are administered to each hemisphere, resulting in a total of 2,000 pulses for the rTMS intervention. Immediately thereafter, the same exercise intervention as the LI-BFRT group was performed.

The RMT will be determined before the start of the intervention. Measurements and interventions were performed using a MagTD transcranial magnetic stimulator (Irid Medical Equipment New Technology Co., Ltd., Wuhan, China) equipped with an aimQ tracking navigation system. Signals will be amplified and band-pass filtered between 20 Hz and 1 kHz, with a sensitivity of 200 μV/div and a sampling rate of 5 kHz. Subjects were instructed to maintain complete relaxation of the target muscle during stimulation and confirm the absence of background activity via real-time EMG feedback. First, activate the MEPs monitoring module. Surface electromyography (EMG) of the abductor pollicis brevis muscle is recorded using dedicated electrode wires. Align the center of the “8-shaped” coil with the representative region of the cerebral cortex associated with the hand function, ensuring the coil is tangent to the skull surface at a 45° angle. Subsequently, sTMS to observe reactive movements in the affected fingers. The RMT is defined as the minimum magnetic stimulation intensity required to elicit MEPs greater than 50 μV in at least 5 out of 10 consecutive sTMS stimuli while the thenar muscle is in a relaxed state.

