### Statistical analysis

2.8

All data were analyzed using SPSS Statistics version 26 (SPSS Inc., USA). Continuous variables are presented as mean ± standard deviation. Baseline characteristics were compared using one-way ANOVA for normally distributed data or the independent-samples rank-sum test/chi-square test for non-normal or categorical data. Intervention effects over time were assessed using two-way repeated-measures ANOVA (time × group) across three time points (baseline, post-intervention, and long-term follow-up). Significant interactions were followed by Bonferroni-corrected pairwise comparisons. Pearson correlation was used to explore relationships between changes in cortical excitability, serum biomarkers, and muscle mass or functional outcomes. Potential synergistic effects of rTMS and LI-BFRT were further evaluated using factorial ANOVA, with significance set at *P* < 0.05.

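### MEP analysis: baseline adjustment depends on an undefined 15% gap that only chance produces between randomised arms, and the assessment intensity is left as a range

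*Protocol article*

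**What the plan says.** Section 2.6.2.2.5 of the protocol article defines the measure: "Six consecutive pulses were applied at 5-s intervals, with the mean amplitude serving as the excitability index". The stimulus is delivered "using the MagTD device at 100%–120% of each participant's resting motor threshold", a range with no single value named. The section continues: "To account for inter-individual variability, MEPs were normalized to baseline values". The adjustment rule follows: "If baseline variability exceeded 15% between groups, analyses were adjusted using either stratification or ANCOVA with baseline MEPs as a covariate". It does not say whether the 15% refers to means or to spread, which of the three arms are compared, what the denominator is, or what decides between the two methods.

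Section 2.8 gives one general model: "Intervention effects over time were assessed using two-way repeated-measures ANOVA", time by group, with baseline as one of the three time points. The same section correlates changes in cortical excitability with serum markers, muscle mass and function.

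Section 2.5.2 says of the threshold: "The RMT will be determined before the start of the intervention". Table 1 marks the RMT test at Week 0 only, but the MEP test at Weeks 0, 12 and 24. It lists MEPs as a secondary outcome. Section 2.7 plans 18 women per arm.

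**The concern.** Three features of the stated rule cause difficulty.

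- **Trigger.** Whether to adjust, and how, is settled only once the baseline data are seen. With concealed randomisation a gap between arms at baseline is chance, so the trigger carries no information about whether adjustment is needed. Baseline adjustment is worth having whenever baseline predicts follow-up, whatever the gap.
- **Normalisation.** A ratio to baseline looks as if it deals with differences between women, but it still depends on the baseline value. It also fits poorly with a model that has baseline as a time point.
- **Intensity.** RMT is defined in section 2.5.2 as the lowest intensity giving MEPs above 50 μV in at least 5 of 10 pulses. The lower end of the range is therefore at threshold and the upper end above it, so amplitude can be expected to depend on the setting.

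The trial's rationale is that rTMS raises motor cortex excitability. MEP amplitude is the only repeated direct measure of this in Table 1, and it feeds the planned correlations. An imprecise or loosely specified MEP analysis weakens the evidence on mechanism.

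**Working it through.** The plan states no figure for how often the trigger fires, so there is none to reproduce.

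**1. How often chance alone fires the trigger**

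Inputs: threshold 0.15 (section 2.6.2.2.5) and n = 18 per arm (section 2.7). The between-woman CV of MEP amplitude is not given, so a range is assumed. Reading used: largest minus smallest arm mean, divided by the overall mean.

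Each arm mean has relative standard error CV/√18. The trigger fires when the range of three independent standard normal values exceeds q = 0.15 × √18 / CV = 0.636 / CV. The table shows this and a simulation with lognormal amplitudes (100,000 runs).

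| CV (assumed) | q | Normal means | Lognormal amplitudes |
|---|---|---|---|
| 0.2 | 3.18 | 6.3% | 6.3% |
| 0.3 | 2.12 | 29.0% | 29.1% |
| 0.4 | 1.59 | 49.9% | 49.4% |
| 0.6 | 1.06 | 73.4% | 73.0% |
| 1.0 | 0.64 | 89.4% | 88.5% |

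The reading matters. For one given pair of arms the lognormal figure at CV 0.3 is 13%. If the 15% is taken literally as a difference in SD or CV between arms, the trigger fires in 83% to 95% of trials at CV 0.2 to 0.8. With 14 per arm (42/3, the number before attrition), the range-of-means figures are 12% at CV 0.2 and 38% at CV 0.3.

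**2. Whether the ratio removes dependence on baseline**

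Let log baseline and log follow-up have equal variance and correlation ρ (assumed). With no treatment effect, the correlation of log(follow-up/baseline) with log baseline is −√((1 − ρ)/2):

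- ρ = 0.3: −√0.35 = −0.59
- ρ = 0.5: −√0.25 = −0.50
- ρ = 0.7: −√0.15 = −0.39

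The ratio over-corrects: a woman with a high baseline tends to have a low ratio.

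**3. What the rule costs**

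Two arms of 18 were simulated (20,000 runs, lognormal amplitudes, effect 0.4 on the log scale, a ratio of e^0.4 = 1.49; all assumed). The conditional rule was a t-test on the ratio, replaced by ANCOVA of the ratio on baseline when the two baseline means differed by more than 15% of their average. The stratification option was not simulated.

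| CV, ρ | Ratio, unadjusted | Conditional rule | Ratio, always adjusted | Log MEP, always adjusted |
|---|---|---|---|---|
| 0.3, 0.5 | 0.973 | 0.980 | 0.991 | 0.996 |
| 0.5, 0.3 | 0.496 | 0.526 | 0.597 | 0.719 |
| 0.5, 0.5 | 0.646 | 0.679 | 0.726 | 0.798 |
| 0.5, 0.7 | 0.870 | 0.886 | 0.900 | 0.924 |
| 0.8, 0.5 | 0.318 | 0.335 | 0.360 | 0.473 |

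At CV 0.5 and ρ 0.5 the conditional rule falls short by 0.798 − 0.679 = 0.119. Of this, 0.726 − 0.679 = 0.047 comes from not always adjusting, and 0.798 − 0.726 = 0.072 from using the ratio instead of the log scale.

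Type I error over CV 0.3, 0.5, 0.8 and ρ 0.3, 0.5, 0.7 was 0.034 to 0.045 for the conditional rule (0.038 at CV 0.5, ρ 0.5) and 0.046 to 0.052 for the log ANCOVA. If an analyst could report the better of the adjusted and unadjusted ratio results, it was 0.059 to 0.073.

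**4. The normalised value in the general model**

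Baseline divided by itself is 1 for every woman. If normalised MEPs enter the three-time-point ANOVA of section 2.8, the baseline visit has no variance.

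**5. The assessment setting**

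The intensity is a range relative to RMT, RMT is marked at Week 0 only, and MEPs are taken at three visits. The text does not say whether one setting is kept for each woman, or whether the later settings refer to the Week 0 RMT or to a new one.

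**The case against.** The best defence is that the rule looks only at baseline data, that section 2.6.2.2.5 gives MEPs their own handling, and that section 2.4 keeps assessors and data analysts blind to allocation. MEPs are also secondary, and a condensed article may leave the stimulus setting to the full protocol. Much of this stands, and it limits the point in several ways:

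- **Type I error.** A reader might infer that a data-dependent trigger inflates it. The simulations show the opposite for the rule itself. Inflation, and then only to about 0.07, needs an analyst who chooses between results.
- **Adjusting a ratio for its own baseline.** A reader might call this a fault in itself. It is not: the ratio already depends on its denominator, and the covariate removes the linear part of that dependence. On the log scale, log(F/B) = a + τG + c·log B rearranges to log F = a + τG + (1 + c)·log B, with the same group effect τ. The fault is that adjustment is conditional.
- **Comparability across visits.** A reader might infer that the visits are not comparable. The text does not say that a woman's setting changes between visits; it only fails to say that it is kept.
- **The zero-variance baseline.** Section 2.8 does not say that normalised MEPs enter the general model, so this problem is conditional.
- **Firing rate.** At a CV of 0.2 the trigger seldom fires on the range-of-means reading, and the rate does not by itself measure harm.

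The defence does not answer the main point. The article states a rule rather than leaving one to be written, and that rule lets chance choose between models with an undefined criterion and two unranked methods.

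**Conclusion.** The point holds in a limited form and should be acted on. The 15% trigger responds only to chance, leaves the model open until baseline data are seen, and loses power against a single analysis that always adjusts.

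The firing rates rest on assumed CVs and on one reading of an undefined criterion. The power figures come from a two-arm comparison with lognormal amplitudes, a shape that favours the log analysis. The size of the loss varies widely with CV and ρ, from 0.016 at CV 0.3, ρ 0.5 to 0.193 at CV 0.5, ρ 0.3 among the cases shown. The direction is the same in every case.

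On intensity, the documents support no more than that comparability across visits is not ensured. The cost falls on the mechanistic evidence.

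**What to change.** 1. Delete the 15% trigger, the choice between stratification and ANCOVA, and the normalisation to baseline.
2. Analyse log MEP amplitude at Weeks 12 and 24 with log baseline MEP as a covariate in every analysis. State that this replaces the general repeated-measures ANOVA for this outcome, and say how a mean amplitude of zero is handled, since its log is undefined.
3. State one assessment intensity for all women and all visits, and say whether it refers to the Week 0 RMT or to one measured again at each visit. Make Table 1 agree. If testing has begun, keep each woman's own baseline setting at her remaining visits.

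Items 1 and 2 cost only wording in the protocol or SAP and remain possible whatever has been collected. Item 3 is wording too if the Week 0 RMT is the reference; a repeated RMT would add a test at Weeks 12 and 24. Parts of the article are in the past tense. If baseline MEPs have already been recorded, item 3 can improve only the visits still to come, and it needs the settings used to be on record.

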##### Hematological parameters

2.6.2.3

Blood samples will be collected from each participant's upper arm vein by professional medical staff before baseline (Week 0) and after the intervention (Week 12). Participants will be required to fast for 12 h before blood collection. Blood will be collected using separator tubes (5 ml), allowed to stand at room temperature for 30 min, and then centrifuged in a centrifuge for 15 min to separate serum and plasma. The centrifuge will be set to 4°C and 3,000 rpm. The serum will be aliquoted into EP tubes and frozen at −80°C for analysis. Blood markers include: creatine kinase (CK), insulin-like growth factor 1 (IGF-1), myostatin, interleukin-6 (IL-6), total testosterone (TT), estradiol (E2), neurofilament light chain (NfL), and C-terminal agrin fragment (CAF).

### Sample size estimation

2.7

Sample size estimation was performed using G*Power 3.1. Based on a previous study (42), the effect size was conservatively estimated to be 0.65, to ensure a conservative and robust study design, we adopted a more cautious effect size of 0.4 in the final calculation. Assuming a one-way ANOVA with three independent groups (1:1:1), a significance level of 0.05 (two-tailed), and a desired statistical power of 0.95, the required total sample size was determined to be 42 participants. With an attrition rate of 20%, a total of 54 participants (18 per group) needs to be recruited.

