**Discussion:**

We have combined central and peripheral motor activation methods for the first time, attempting to use BFRT in combination with rTMS intervention to recruit more motor units by increasing motor cortex excitability, thereby enhancing skeletal muscle motor ability under BFRT and examining the intervention effects on skeletal muscle mass and strength in postmenopausal women. This will provide a new paradigm for healthy intervention in the skeletal muscles of postmenopausal women.

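### The stated 0.95 power is for a one-way three-arm ANOVA and does not describe the Bonferroni-corrected rTMS + LI-BFRT versus LI-BFRT comparison, the only one that isolates rTMS

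*Protocol article*

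**What the plan says.** Section 2.7 of the protocol article bases the sample size on a single test: "Assuming a one-way ANOVA with three independent groups (1:1:1), a significance level of 0.05 (two-tailed), and a desired statistical power of 0.95". It first says "the effect size was conservatively estimated to be 0.65" and then "we adopted a more cautious effect size of 0.4 in the final calculation". The result is 42 evaluable participants, raised to 54 (18 per arm) for 20% attrition.

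Section 2.8 does not use a one-way ANOVA for efficacy; it appears there only for baseline characteristics. The efficacy analysis reads "Intervention effects over time were assessed using two-way repeated-measures ANOVA (time × group) across three time points", and then "Significant interactions were followed by Bonferroni-corrected pairwise comparisons". A factorial ANOVA is added to look for synergy between rTMS and LI-BFRT. No power is given for any pairwise comparison.

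The rationale in the abstract's Discussion is "attempting to use BFRT in combination with rTMS intervention to recruit more motor units by increasing motor cortex excitability". Section 2.4 lists three arms: rTMS + LI-BFRT, LI-BFRT and control. Section 2.5.2 gives the combined arm the same exercise as the LI-BFRT arm.

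**The concern.** A one-way ANOVA with three arms is a 2-df test that the arm means are not all equal. It can be significant because both training arms beat health education, and that says nothing about rTMS. What rTMS adds shows only in rTMS + LI-BFRT versus LI-BFRT, since those two arms differ by rTMS alone. The factorial ANOVA cannot supply this information: without an rTMS-only arm, the interaction of rTMS with LI-BFRT is not estimable.

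The power printed in 2.7 is therefore for a test that 2.8 does not use for efficacy, and it does not carry over to the comparison that bears on the trial's rationale. A reader who takes 0.95 as the chance of detecting an rTMS effect could read a non-significant contrast as good evidence that rTMS adds nothing.

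**Working it through.** **Inputs.** From 2.7: three equal arms, alpha 0.05, target power 0.95, effect sizes 0.4 and 0.65 (read as Cohen's f, the measure G*Power uses for a one-way ANOVA), N = 42 evaluable (14 per arm) and 54 recruited (18 per arm). From 2.8: Bonferroni pairs. Assumed here: three arm pairs, so alpha = 0.05/3 = 0.0167; a common SD; pooled error df.

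**1. The plan's own figure.** Omnibus power uses the noncentral F with λ = N·f² and df 2 and N − 3.

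| f | N | λ | power |
|---|---|---|---|
| 0.65 | 42 | 42 × 0.4225 = 17.75 | 96.1% |
| 0.40 | 42 | 42 × 0.16 = 6.72 | 60.0% |
| 0.40 | 54 | 54 × 0.16 = 8.64 | 72.6% |
| 0.40 | 102 | 102 × 0.16 = 16.32 | 95.5% |

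The smallest balanced N for 95% power is 42 at f = 0.65 and 102 at f = 0.4. So 42 reproduces only with the effect size that the text says was replaced. The attrition step is consistent: 42/0.8 = 52.5, so 53, rounded up to 54 for equal arms.

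**2. From f to the rTMS difference.** The value of f does not fix any single pair; the pattern of means does.
- Equal spacing (control < LI-BFRT < combined), means −d, 0, d: f² = 2d²/3, so d = f√1.5. This gives 0.796 SD at f = 0.65 and 0.490 SD at f = 0.4.
- Only the combined arm differs, means 0, 0, d: f = d√2/3, so d = 3f/√2. This gives 1.379 SD and 0.849 SD.

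**3. Power for the pair, single-time SD.** Noncentral t with noncentrality d√(n/2) and df 3n − 3. At n = 14 the df is 39 and the two-sided critical value at 0.0167 is 2.502.

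| pattern | f | n per arm | noncentrality | power |
|---|---|---|---|---|
| equal spacing | 0.65 | 14 | 0.796 × √7 = 2.11 | 35.8% |
| equal spacing | 0.40 | 14 | 0.490 × √7 = 1.30 | 12.6% |
| equal spacing | 0.65 | 18 | 0.796 × 3 = 2.39 | 47.1% |
| equal spacing | 0.40 | 18 | 0.490 × 3 = 1.47 | 16.7% |
| only combined differs | 0.65 | 14 | 1.379 × √7 = 3.65 | 86.8% |
| only combined differs | 0.40 | 14 | 0.849 × √7 = 2.24 | 40.9% |

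A simulation of 100,000 trials that also required a significant omnibus test gave 35.8% for the first row.

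**4. Power on change from baseline.** Section 2.8 analyses repeated measures, so the single-time SD may be the wrong scale. If f refers to the single-time SD and ρ is the within-person correlation, the change has SD σ√(2(1 − ρ)), and d becomes d/√(2(1 − ρ)). With equal spacing and 14 per arm:

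| ρ | f = 0.65 | f = 0.40 |
|---|---|---|
| 0 | 17% | 7% |
| 0.5 | 36% | 13% |
| 0.7 | 59% | 22% |
| 0.8 | 79% | 34% |

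The documents give no ρ.

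**5. Detectable difference.** With 14 per arm at alpha 0.0167, the pair has 80% power for 1.27 SD and 95% power for 1.59 SD, in SD units of whatever is analysed. For change at ρ = 0.8 these are 1.27 × √0.4 = 0.80 and 1.59 × √0.4 = 1.01 single-time SDs.

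**6. Does correcting the effect size cure it?** No. At N = 102 (34 per arm), f = 0.4 and equal spacing, the noncentrality is 0.490 × √17 = 2.02 and the power is 34%.

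**The case against.** The plan never names rTMS + LI-BFRT versus LI-BFRT as its key test, and section 2.7 openly ties 0.95 to a one-way ANOVA. Nothing in the text claims 0.95 for the rTMS contrast or says that a null result will be read as no effect. This stands. The importance of that pair is inferred from the arms and the rationale, and the misreading is a risk rather than something the plan commits.

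A reader might go further and infer that the trial has 36% power for rTMS and would usually miss a real effect. The documents do not support that. The 36% needs equal spacing and a single-time SD, and neither is stated. The source of 0.65 is not shown, so the SD behind it is unknown. If both open assumptions are favourable, the shortfall goes away: with only the combined arm differing, f = 0.65 and ρ = 0.7, the difference is 1.379/√0.6 = 1.78 change SDs, the noncentrality is 1.78 × √7 = 4.71, and power is 98%.

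A reader might also infer that Bonferroni wastes power because three arms behind an omnibus test form a closed procedure at 0.05 per pair. That holds behind a 2-df between-arm test at Week 12, but the plan's gate is the interaction over three time points. If only Week 24 differs, that gate opens while Week 12 is null. Simulated familywise error of unadjusted Week 12 pairs is then about 12%, against 4.4% with Bonferroni. The correction is doing real work.

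**Conclusion.** The point holds as a misdescription of power. The 0.95 in 2.7 belongs to a test that 2.8 does not use for efficacy. It does not cover the one contrast that isolates rTMS, and even for the omnibus test it is right only at f = 0.65.

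The size of the gap is a range. With 14 per arm and three Bonferroni pairs, equal spacing gives 17% to 79% at f = 0.65 and 7% to 34% at the stated 0.4, for ρ from 0 to 0.8; the single-time values are 36% and 13%. If LI-BFRT does no better than control, the single-time values are 87% and 41%. All of this treats one outcome at one post-baseline time, with a common SD. Change from baseline stands in for the planned repeated-measures pairs.

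The trial can still run as designed. The statement should be corrected because readers will use it to judge a null rTMS result.

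**What to change.** No change in enrolment, and the Bonferroni step stays.

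In section 2.7:
- State the omnibus power together with the effect size that yields it: 96% at f = 0.65 with 42 evaluable; 60% with 42 and 73% with 54 at f = 0.4.
- Say that this power does not cover pairwise contrasts.
- Add the detectable difference for rTMS + LI-BFRT versus LI-BFRT under the Bonferroni comparison of 2.8: about 1.3 SD at 80% power and 1.6 SD at 95% power with 14 per arm. Say which quantity the SD refers to, and state the within-person correlation assumed.

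In section 2.8, commit to reporting that contrast with its confidence interval, and to not reading a non-significant result as no added effect of rTMS.

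The cost is a few sentences and a less favourable power statement. The sponsor must also commit to a correlation, or show a range where none is known.

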### Statistical analysis

2.8

All data were analyzed using SPSS Statistics version 26 (SPSS Inc., USA). Continuous variables are presented as mean ± standard deviation. Baseline characteristics were compared using one-way ANOVA for normally distributed data or the independent-samples rank-sum test/chi-square test for non-normal or categorical data. Intervention effects over time were assessed using two-way repeated-measures ANOVA (time × group) across three time points (baseline, post-intervention, and long-term follow-up). Significant interactions were followed by Bonferroni-corrected pairwise comparisons. Pearson correlation was used to explore relationships between changes in cortical excitability, serum biomarkers, and muscle mass or functional outcomes. Potential synergistic effects of rTMS and LI-BFRT were further evaluated using factorial ANOVA, with significance set at *P* < 0.05.

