### Interventions

2.5

Pre-intervention procedures: Before the intervention, participants in the rTMS + LI-BFRT and LI-BFRT groups underwent a one-repetition maximum (1RM) test and arterial occlusion pressure (AOP) measurement, and were trained to use the 6–20 Borg Rating of Perceived Exertion (RPE) scale to determine target resistance loads. Exercise loads were applied using appropriately weighted dumbbells. Missed sessions were rescheduled within the same week to maintain consistent intervention volume. All participants attended a pre-intervention orientation to familiarize themselves with the procedures.

Adherence and fidelity: All sessions were supervised by trained researchers. Attendance and completion of prescribed exercise sets were recorded digitally. Any missed sessions or protocol deviations were documented. Adherence was calculated as the percentage of completed sessions relative to the total prescribed, with an attendance rate of ≥ 80% considered a valid indicator of intervention effectiveness. Detailed intervention protocols for all groups are provided in Table 2.

**Table 2 T2:** Details of the three groups of protocol.

Weeks	Group	Specific intervention content	Sets	Repetitions	Interval rest time between sets	Intensity	Frequency
1–4	LI-BFRT	Seated biceps curl, Seated shoulder press Seated knee extension, Squat	4	12, 10, 10, 10	30s	Phase 1 20%1RM	3times/week
	rTMS + LI-BFRT	M1 area, at 10 Hz, 90%RMT, intermittent stimulation, a total of 2,000 pulses; LI-BFRT immediately after the stimulation ends.					
	CG	Education session (20 min)	/	/	/	/	1time/week
5–8	LI-BFRT	Seated biceps curl, Seated shoulder press Seated knee extension, Squat	4	12, 10, 10, 10	30s	Phase 2 25%1RM	3times/week
	rTMS + LI-BFRT	M1 area, at 10 Hz, 90%RMT, intermittent stimulation, a total of 2,000 pulses; LI-BFRT immediately after the stimulation ends					
	CG	Education session (20 min)	/	/	/	/	1time/week
8–12	LI-BFRT	Seated biceps curl, Seated shoulder press Seated knee extension, Squat	4	12, 10, 10, 10	30s	Phase 3 30%1RM	3times/week
	rTMS + LI-BFRT	M1 area, at 10 Hz, 90%RMT, intermittent stimulation, a total of 2,000 pulses; LI-BFRT immediately after the stimulation ends					
	CG	Education session (20 min)	/	/	/	/	1 time/week
M1 area: primary motor cortex							

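### The three-visit repeated-measures ANOVA makes poor use of Week 12 and baseline data; a baseline-adjusted mixed model would give about 7 to 10 points more power for the key arm contrast, under assumed inputs

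*Protocol article*

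**What the plan says.** Protocol article, section 2.8: "Intervention effects over time were assessed using two-way repeated-measures ANOVA", with time and group as the two factors and three levels of time, the first of which is baseline. The next step reads: "Significant interactions were followed by Bonferroni-corrected pairwise comparisons". The section does not say what those comparisons are made on. On software: "All data were analyzed using SPSS Statistics version 26".

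Section 2.7 expects losses: "With an attrition rate of 20%, a total of 54 participants (18 per group) needs to be recruited".

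The only baseline-covariate adjustment in the article concerns motor-evoked potentials, a secondary outcome, and it applies only if baseline differs by more than 15% between groups. In that case "analyses were adjusted using either stratification or ANCOVA with baseline MEPs as a covariate". The primary outcomes (muscle cross-sectional area, grip strength, knee-extension strength) have no such provision, although Table 1 schedules all of them at Week 0.

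No visit is labelled primary. The aim at the end of the Introduction concerns the effects of a 12-week intervention, and Week 12 is the end of that intervention.

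**The concern.** Three features of the named model fit this design poorly.

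- **Lost data.** Classical repeated-measures ANOVA needs every level of the within-subject factor. A missing Week 24 value removes the woman's Week 12 value as well.
- **Inefficient use of baseline.** Treating baseline as an outcome level means that the interaction works on change. Unless the correlation between visits is 1, a baseline covariate gives a smaller variance.
- **An unspecified pairwise step.** The contrast that isolates what rTMS adds is rTMS + LI-BFRT against LI-BFRT. It is reached only after an omnibus test that pools Week 12 with Week 24, and the text leaves open whether it compares raw values or change.

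At 18 women per arm, lost precision matters, and all the data needed to recover it are already being collected.

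**Working it through.** **The plan's own figures.** The attrition step reproduces: 42/0.8 = 52.5, so 53, rounded up to 54 for equal arms. Applied to 54, 20% attrition leaves 54 × 0.8 = 43.2 women with all visits. (The 42 itself does not follow from the stated effect size of 0.4 at 95% power, which needs 102. That is a separate matter.)

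**Inputs from the article.** 18 per arm, three arms, 20% attrition, alpha 0.05, Bonferroni correction (three arm pairs, so 0.05/3).

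**Assumed inputs, not in the article.**
- Week 12 means 0, 0.5 and 1.0 SD for control, LI-BFRT and rTMS + LI-BFRT. Their spread is √[(0.25 + 0 + 0.25)/3] = 0.41 SD, close to the 0.4 in section 2.7. The contrast of interest is 0.5 SD.
- Equal correlation ρ between visits, from 0.5 to 0.9.
- Share of the effect kept at Week 24: none, half or all.
- Random dropout: 10% before Week 12 and 11.1% of the rest before Week 24. This leaves 54 × 0.9 = 48.6 women at Week 12 (16.2 per arm) and 48.6 × 0.889 = 43.2 at Week 24 (14.4 per arm). About 5 women would be measured at Week 12 and then dropped from its analysis.

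**Variance of an arm difference** (SD = 1, n per arm):
- raw Week 12: 2/n
- change from baseline: 4(1 − ρ)/n
- baseline-adjusted: 2(1 − ρ²)/n

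The ratio of adjusted to change is (1 + ρ)/2: 0.75, 0.85, 0.90 and 0.95 at ρ = 0.5, 0.7, 0.8 and 0.9. At ρ = 0.8 that cuts the standard error by about 5% (√0.90 = 0.95). Against raw values the ratio is 1 − ρ² = 0.36, a 40% cut.

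**Hand check.** Power ≈ Φ(0.5/SE − c). The Bonferroni critical value c is about 2.50 for completers (n = 14.4) and 2.49 for all women with Week 12 data (n = 16.2).

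| ρ | Change, completers: 0.5/SE → power, no gate | Adjusted, all Week 12: 0.5/SE → power |
|---|---|---|
| 0.5 | 1.34 → 12% | 1.64 → 20% |
| 0.7 | 1.73 → 22% | 1.99 → 31% |
| 0.8 | 2.12 → 35% | 2.37 → 45% |
| 0.9 | 3.00 → 69% | 3.26 → 78% |

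For raw Week 12 values among completers, SE = √(2/14.4) = 0.373 and 0.5/SE = 1.34, so power is about 12% whatever ρ is.

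**Simulation of the full procedure, gate included:**

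| ρ | Gate, then change | Adjusted, all Week 12 data | Gate, then raw Week 12 |
|---|---|---|---|
| 0.5 | 12–13% | 20% | about 10–15% throughout |
| 0.7 | 21–23% | 31% | |
| 0.8 | 34–36% | 44% | |
| 0.9 | 68% | 77% | |

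**Where the gain comes from at ρ = 0.8.** Gate-then-change gives 35–36%. Ungated adjusted analysis of the same completers gives 38–39%. Adding the women seen at Week 12 but not at Week 24 brings about 6 points more. The interaction was significant in 92% of trials if half the effect is kept at Week 24, in 98% if all or none is kept, and in about 100% at ρ = 0.9. At ρ = 0.6 it was significant in only 62–77%.

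**The case against.** The strongest reply is that the loss is modest and depends on inputs that the article does not give. On the omnibus tests alone, with an effect of 0.4 at Week 12, the interaction has 51–65% power against 80–81% for Week 12 ANCOVA at ρ = 0.5, but both reach about 100% at ρ = 0.9. That is correct for the omnibus tests. The pairwise contrast still gains about 9 points at ρ = 0.9, mainly because more women are analysed.

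A reader might infer stronger points that the documents do not support:

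- **That power falls to 10–15%, or that adjustment cuts the standard error by 40%.** Both hold only if the pairwise step compares raw Week 12 values. That reading is plausible but not stated. Against change scores the gain is 7 to 10 points.
- **That the plan ignores baseline.** The time × group interaction is unaffected by constant baseline shifts, so baseline is used, only less efficiently than as a covariate.
- **That the plan prescribes deletion of incomplete cases.** No such rule is written. Deletion follows from the method as normally run, and an unseen analysis plan could provide imputation.
- **That the result will be biased.** Bias would need dropout related to response or tolerance. The simulated dropout was random, so no bias has been shown.
- **That the attendance statement, "with an attendance rate of ≥ 80% considered a valid indicator of intervention effectiveness", restricts the analysis.** It describes adherence and defines no analysis set.
- **That Week 12 is the declared primary visit.** This is an inference from the aim.

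**Conclusion.** The point holds as one of efficiency and specification. The named model, run in the usual way, discards Week 12 data from women lost later, uses baseline less well than it could, and leaves the decisive arm comparison undefined. Against the more favourable reading (change scores), the cost is about 7 to 10 percentage points of power for rTMS + LI-BFRT against LI-BFRT at every correlation from 0.5 to 0.9. Against the raw-value reading it is larger and grows with the correlation. The gate itself costs little at ρ of 0.8 or above.

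These sizes rest on the assumed Week 12 means, equal correlations and random dropout timing. The direction does not depend on the exact values: the adjusted variance is never larger than that of change, and using all Week 12 data never leaves fewer women.

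**What to change.** Replace the repeated-measures ANOVA for the primary outcomes with a linear mixed model (SPSS MIXED):

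- Outcomes: the Week 12 and Week 24 values.
- Fixed effects: arm, visit, arm × visit, baseline, baseline × visit.
- Covariance: unstructured.
- Population: all randomised women with any post-baseline value, in their assigned arm.

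Name Week 12, the end of the intervention, as the primary time point. Test its arm contrasts without the interaction gate, keep the Bonferroni correction across the three contrasts, and report Week 24 as secondary. The correction must be stated once the gate goes. It does not settle multiplicity across the four primary measures in Table 1, which needs its own rule.

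The cost is a change of wording, with the same software, visits and data. The small downside is reliance on a missing-at-random assumption.
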